## Abstract

**Background::**

High blood pressure (HBP) is a multifactorial clinical condition, with a high morbidity and mortality rate and low rates of control. Due to its high prevalence, it is necessary to search for methods which aim to improve the quality of life of hypertensive patients. Studies have shown that low level laser therapy (LLLT) is capable of inducing a photobiological response within the cells which modifies the micro and macrovascular response; this accompanies evidence showing the systemic effects of intravascular laser irradiation of blood (ILIB). In the hypothesis that the use of LLLT can influence blood pressure levels, and perhaps facilitate adherence to treatment, this study aims to present a clinical research protocol with the goal of determining the effect of photobiomodulation in relation to changes in the hemodynamic parameters of hypertensive and normotensive patients.

**Method::**

Forty-four participants, frequent attendees of an ambulatory university clinic, will be subdivided into 4 groups, and then submitted to protocol sessions of ILIB. The technique is noninvasive and consists of a laser which is attached to a bracelet which has been specifically developed for the light beam to be transcutaneously carried over the radial artery. Before the procedure, at the end of the photobiomodulation cycles, and 1 month after the end of therapy, blood samples will be collected for the evaluation of C-reactive protein, interleukin 6, and nitric oxide, to be analyzed by immunoturbidimetric, ELISA, and Griess reactions, respectively.

**Analysis of results::**

Results will be analyzed using descriptive and inferential statistics and will be compiled into tables and/or graphs, with the help of SPSS version 24.0 with the adopted significance level for all tests being α = 0.05.

**Discussion::**

The treatment of HBP involves both pharmacological and nonpharmacological therapy. Animal studies with photobiomodulation have previously shown hypotensive effects. Gaps in the literature exist regarding the applicability of this nonpharmacological therapy in humans. This study aims to consider the possibility of offering nonpharmacological therapy to hypertensive patients with the goal of increasing adherence to the treatment as well as minimizing morbidity and mortality caused by hypertension.

## Introduction

1

High blood pressure (HBP) is a clinical condition of multifactorial origin and metabolic alterations. Considered a global public health problem unsatisfactorily controlled, it represents the most prevalent vascular disease in the world. Characterizing one of the principle modifiable risk factors and main underlying cause of death due to cardiocerebrovascular disease, its prevalence is also reflected in high hospital admission rates and its high costs to public coffers.^[1–6]^

Blood pressure (BP) control is one of the most complex physiological functions of the organism. It depends on the integration of the cardiovascular, renal, neural, and endocrine systems, ^[7,8]^ acting together to maintain control of cardiac output and peripheral vascular resistance. The manifestation of hypertension is therefore necessarily related to changes in these parameters. ^[9,10]^

Systemic vascular resistance is mainly regulated in the regions of the arterioles and is influenced by neural and hormonal factors. The normality of vascular tone comes from the balance between circulating factors that induce vasoconstriction (such as angiotensin II and catecholamines) and vasodilation (such as kinins, prostaglandins, and nitric oxide [NO]). Other factors are also involved in this process, such as pH, hypoxia, and neural interactions (α and β adrenergic systems).^[11]^

Endothelial lesions result in an inflammatory response, with the performance of various cell types (lymphocytes, monocytes, platelets, and smooth muscle cells), ^[12]^ causing endothelial cell dysfunction, vascular wall stiffening, and atherosclerosis plaque formation.^[13]^ These endothelial lesions and complications are confirmed by inflammatory markers that result in endothelial activation, such as C-reactive protein (CRP) and interleukin 6 (IL-6), ^[14,15]^ this last 1 correlating positively with systolic and diastolic pressures. Acting in conjunction with these for BP control, the kidney also produces several vasorelaxative and antihypertensive substances (such as prostaglandins and NO), which balance the vasoconstricting action of angiotensin II.^[8,9,10]^

Currently, the treatment of hypertension is based on a nonpharmacological and pharmacological combination, aimed at implanting strategies that may reverse or prevent the progression of these factors, as well as the prescription of drugs with vasodilatory actions, beta blockers, and diuretics, leading to a decrease in BP.^[11,16]^ It should be emphasized that the use of drugs can cause the manifestation of signs and symptoms which are the result of adverse or collateral effects. This in turn may influence the patient's adherence to treatment, which consists in the acceptance of and obedience to what was prescribed and directed by the attending healthcare professional.^[17]^ Non-adherence is identified as the main cause of uncontrolled arterial hypertension ^[18]^ therefore it becomes imperative to find methods which facilitate this process with the purpose of promoting improvement in the quality of life of these patients.

Low intensity laser therapy, or photobiomodulation, is capable of inducing a photobiological response inside the cells; activating the production of adenosine triphosphate (ATP), NO, and reactive oxygen species; and altering sodium–potassium pumps and calcium channels in cell membranes, ^[19]^ as well as proving to be an efficient, noninvasive, low cost, safe tool.

Among the different methods of photobiomodulation, intravascular laser irradiation of blood (ILIB) has been shown to prompt systemic effects. ILIB has been studied since 1981 by Soviet scientists; it was developed for the treatment of cardiovascular diseases with evidence of improved blood rheological properties and microcirculation as well as reduction in the infarct area, cardiac arrhythmias, and sudden death. ^[20]^

In view of the above, the verification of the effects of systemic photobiomodulation on the control of BP in humans shows itself to be a current, relevant, promising area of study, principally in order to prevent patients’ health problems and the consequent high cost to public health, along with minimizing the gaps in the literature in this area.

Will be a study single-center, controlled, randomized, blinded clinical trial whose general objective will be to evaluate the effects of systemic photobiomodulation on the hemodynamic variables of hypertensive patients (the primary outcome variable will be BP values). Besides, will be analyzed the dosages of IL-6, CRP, and NO.

## Methodology/design

2

### Description of the proposed study

2.1

It is a single-center, controlled, randomized, blinded clinical trial outlined in accordance with the criteria set out by the SPIRIT statement. The sample will consist of 44 participants in medical follow-up at the Nove de Julho University Integrated Outpatient Healthcare Clinic located in the city of São Paulo, Brazil, from March 2019 to August 2019.

After verbal and written explanation, individuals who agreed to participate in the study will sign the Free and Informed Term of Consent already approved by the Nove de Julho University's Research Ethics Committee registered under CAAE 85714318.3.0000.5511.

### Clinical trial registry

2.2

The protocol for this study was registered in the Brazilian Registry of Clinical Trials—ReBEC (RBR-7n55nz), first received in February 2019, http://www.ensaiosclinicos.gov.br/rg/?q=RBR-7n55nz.

### Sample size

2.3

The determination of the number of patients necessary was calculated using G ∗ Power software (version 3.1.9.2, Franz Faul, Universität Kiel, Germany), in which the values for the mean and standard deviation of the primary outcome variable (systolic or diastolic BP) came from the article by Pereira et al.^[21]^ The calculation was performed using the ANOVA repeated measures, with a significance of 5% and power of test at 95%. According to sample calculation, 44 hypertensive patients will be divided into 4 groups with 11 individuals each.

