**Figure 1 F1:**
[figure not shown]
Flowchart describing study design, sample composition, and experimental protocol.

Research will be carried out to evaluate the effects of photobiomodulation using 2 ILIB protocols established by the manufacturer of the laser equipment: 60 minutes daily exposure time (Laser 60) and 30 minutes daily exposure time (Laser 30), with respective placebo groups (Placebo 60 and Placebo 30):

Laser 60 (N = 11): will be submitted to the conventional drug treatment previously instituted and ILIB sessions for 60 minutes daily for 5 days, to be repeated after 20 days and, after completing 3 cycles, the patients will be reevaluated 1 month after the end of the proposed therapy.Placebo 60 (N = 11): will be submitted to the conventional drug treatment previously instituted and placebo sessions of ILIB for 60 minutes daily for 5 days, to be repeated after 20 days and, after completing 3 cycles, the patients will be reevaluated 1 month after the end of the proposed therapy. The placebo will be performed by placing a beam obturator at the laser output, so that all noise from the equipment will remain the same as that of the Laser 60 group, but no radiation will be delivered to the target.Laser 30 (N = 11): will be submitted to the conventional drug treatment previously instituted and ILIB sessions for 30 minutes daily, for 10 days, being repeated after 20 days and, after completing 3 cycles the patients will be reevaluated 1 month after the end of the proposed therapy.Placebo 30 (N = 11): will be submitted to the conventional drug treatment previously instituted and ILIB sessions for 30 minutes daily, for 10 days, being repeated after 20 days and, after completing 3 cycles, the patients will be reevaluated 1 month after the end of the proposed therapy. The placebo will be performed with the same obturator method mentioned previously.

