### Outcomes

2.7

Measurements of BP (primary outcome) and heart rate will be performed before, during (every 5 minutes), and at the end of each session, being measured again in the follow-up.

Blood will be collected from all participants to measure the dosage of IL-6, CRP, and NO. Collection will be performed at the beginning of the study and before each cycle (BASELINE—B1, B2, B3), at the end of each cycle of photobiomodulation (END—E1, E2, E3) and 1 month after the end of the proposed therapy (FL-UP). In total, there will be 7 samples from each patient.

Serum samples will be collected in two 10 mL dry tubes and will be processed in a centrifuge at 1000 rpm for 5 minutes and the plasmas at the top of the tubes will be withdrawn and centrifuged again to obtain clear plasmas. The samples will be stored in a freezer at −80° C until the analyses are performed.

The CRP analysis will be performed by means of the immunoturbidimetric test, which allows the quantification of the CRP concentration present in the sample when following the protocol established by the kit manufacturer. IL-6 analysis will be performed via the ELISA method with the use of a specific kit (Human IL-6 ELISA MAX Deluxe, BioLegend, San Diego). The concentration of NO will be determined using a specific kit (Total NO and Nitrite/Nitrite Parameter Assay Kit), where nitrite/nitrate concentration will be determined via the Griess reaction after enzymatic reduction of nitrate in nitrite with the nitrate reductase enzyme in a reduction solution. This procedure will be in accordance with those recommended by the manufacturers.

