### Analysis and publication of data

2.9

After data collection, the data will be grouped into categories using Microsoft Office Excel 2007 (Redmond). The data will be analyzed using descriptive and inferential statistics and compiled into tables and/or graphs with the help of SPSS version 24.0 (IBM, New York). If the data are normal, parametric tests will be used to test inter and intragroup differences.

If they are not normal, nonparametric tests will be used. The level of significance adopted for all tests will be α = 0.05. The data will be protected in a spreadsheet and in a cloud under the care of the researchers. After the study, the same will be presented for publication in the form of a scientific article, where readers will have access to the results obtained in this research.

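### No single blood-pressure component, time and contrast is named as primary, yet every test is set at 0.05, so nothing carries the stated 5% error rate

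*Protocol article*

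**What the plan says.** The protocol article describes the primary outcome in three places.

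- Introduction: "the primary outcome variable will be BP values", with no component or time.
- Section 2.3 (Sample size): the calculation used the "mean and standard deviation of the primary outcome variable (systolic or diastolic BP", from a cited article. The method was repeated-measures ANOVA at 5% significance and 95% power, giving 44 patients in four groups of 11.
- Section 2.7 (Outcomes): "Measurements of BP (primary outcome) and heart rate will be performed before, during (every 5 minutes), and at the end of each session", and once more at follow-up.

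Section 2.6 gives the session schedule. The 60-minute arms have "ILIB sessions for 60 minutes daily for 5 days, to be repeated after 20 days and, after completing 3 cycles" and the 30-minute arms have "ILIB sessions for 30 minutes daily, for 10 days, being repeated after 20 days and, after completing 3 cycles". Each laser arm has a placebo arm of the same session length.

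On analysis, section 2.9 says that, if the data are normal, "parametric tests will be used to test inter and intragroup differences", and that otherwise nonparametric tests will be used. It adds: "The level of significance adopted for all tests will be α = 0.05".

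**The concern.** A 5% error rate belongs to a defined test. Here the component is an either/or, the primary label covers every reading in the schedule, four arms allow several contrasts, and each test has its own 0.05. Results for systolic pressure in one regimen, diastolic pressure in the other, or a change within one arm could all be reported as the primary result.

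Two things are at stake. The first is the false-positive rate of the trial's main conclusion. The second is the link between sample size and result: if section 2.3 does not say which pressure supplied the mean and standard deviation, the stated 95% power cannot be attached to whichever pressure is reported.

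This is more than detail left to an analysis plan. Naming the primary endpoint is the protocol's task, and the article itself fixes both the either/or and the uniform 0.05.

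**Working it through.** **Inputs from the protocol article.** Sessions and arms (section 2.6), reading schedule (2.7), 11 per arm (2.3), 0.05 per test (2.9).

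**Assumptions.** One follow-up reading; correlation between systolic (SBP) and diastolic (DBP) pressure of 0.5-0.8; equal correlation between times of 0.5-0.9. The article gives none of these.

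**1. The plan's own figure, N = 44.** It cannot be reproduced, because the effect size f, number of measurements m, correlation ρ and ANOVA effect are not stated. Noncentral-F power was used with four groups and α = 0.05. The noncentrality is λ = f²Nm/(1−ρ) for the within-subject and interaction effects, and λ = f²Nm/(1+(m−1)ρ) for the between-group effect. For m = 2-7 and ρ = 0.5-0.7, 95% power at N = 44 needs:

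- between groups: f about 0.50-0.61
- within subjects: f about 0.14-0.28
- group-by-time interaction: f about 0.18-0.33

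One assumed set returns exactly 44: the within-subject effect with f = 0.25, m = 3, ρ = 0.5, where λ = 0.0625 × 44 × 3 / 0.5 = 16.5 on 2 and 80 degrees of freedom and power is 0.955. With the same values, power is 0.850 for the interaction and 0.337 for the between-group effect. So 44 is not shown to be wrong, but what it supports depends on which effect was meant.

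**2. Readings under the primary label.**

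- 60-minute arms: before + 11 interim + end = 13 per session. Sessions: 5 × 3 = 15. 13 × 15 = 195, plus follow-up = 196.
- 30-minute arms: before + 5 interim + end = 7 per session. Sessions: 10 × 3 = 30. 7 × 30 = 210, plus follow-up = 211.

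Each reading yields an SBP and a DBP value.

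**3. Chance of at least one false positive, either pressure sufficing.** For independent tests at one time: one contrast 1 − 0.95² = 0.0975; both laser-versus-own-placebo contrasts 1 − 0.95⁴ = 0.185. For correlated readings, a null simulation was run (11 per arm, two-sided t-tests at 0.05, 10,000 runs per setting):

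| Analysis times | One contrast | Both contrasts |
|---|---|---|
| 1 | 0.079-0.097 | 0.154-0.180 |
| 4 | 0.148-0.279 | 0.274-0.477 |

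The low ends come from the highest correlations (0.8 between pressures and, for four times, 0.9 between times). The high ends come from 0.5 for both. The four times could be the ends of cycles 1-3 and follow-up. That choice is an assumption: section 2.7 defines end-of-cycle points for blood samples, not for blood-pressure analysis.

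**4. If repeated-measures ANOVA were the analysis.** One omnibus test per pressure at 0.05 means two tests, so at most 0.10, and 0.0975 if independent.

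**The case against.** The strongest reply is that the article never says one significant result makes the trial positive. A reader might infer that from the uniform 0.05, but the text only leaves the matter open. An analysis plan or the registry record, neither of which is at hand, could narrow the choice. This stands as a limit on the claim. It does not repair the either/or in section 2.3.

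Second, the article plans no set of 16 t-tests (4 times × 2 pressures × 2 contrasts). The only inferential method it names is repeated-measures ANOVA, which handles several times in one model. This also stands: the four-time figures are conditional, and a false-positive rate near one half should not be read as a property of the plan. Yet section 2.9 does not fix the ANOVA as the analysis, and even one omnibus test per pressure allows up to about 10%.

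Third, a reader might infer that the unequal session lengths leave the arms without a common time axis, or that resting during sessions distorts the comparison. The documents do not support either as a defect. Pre-session, end-of-session and follow-up readings exist in all four arms, and each laser arm has a duration-matched placebo exposed to the same rest. The five-minute readings may also serve safety, since section 2.8 anticipates falls in pressure during therapy.

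**Conclusion.** The point holds in a limited form. The primary outcome is stated as systolic or diastolic, spread over all readings and tested at 0.05 throughout, so no single component, time and contrast carries the 5% error rate. The either/or alone takes the rate to about 8-10% for one contrast at one time, and to about 15-18% when both laser-versus-own-placebo contrasts count. These figures assume that either pressure suffices and that the two are correlated 0.5-0.8. The 27-48% range further assumes four analysis times, separate t-tests and between-time correlations of 0.5-0.9. Every scenario examined with either pressure sufficing exceeds 5%. The check does not show N = 44 to be wrong.

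**What to change.** Before unblinding, amend the protocol and registry entry as follows.

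- **Component and time.** Name one pressure (for example SBP) at one time or summary shared by all four arms as the sole primary endpoint. A resting reading at the end of the last cycle or at the 1-month re-evaluation would do. Adjust for the pre-treatment value, and define both readings. Which pressure and time to choose is the investigators' decision; the documents do not settle it.
- **Contrast.** State either one pooled laser-versus-placebo test stratified by regimen at two-sided 0.05, or the two laser-versus-own-placebo contrasts with Holm adjustment. The second is closer to section 2.6, which sets two regimens against their respective placebos.
- **Everything else.** Make the other pressure, in-session readings, heart rate, biomarkers and within-group tests secondary or descriptive.
- **Section 2.3.** State which pressure and which ANOVA effect N = 44 was based on, and give the power of the chosen primary test.

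The cost goes beyond wording. Fewer results can be claimed at 5%, and a single-time comparison replaces the repeated-measures basis of the sample size, so the 95% power may have to be restated less favourably. By normal approximation, 95% power at two-sided 0.05 needs a difference of (1.960 + 1.645) × √(2/11) = 1.54 residual standard deviations for one contrast of 11 against 11, or 3.605 × √(2/22) = 1.09 for the pooled 22 against 22. Baseline adjustment reduces the residual standard deviation by an amount the article does not allow one to calculate.

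If the investigators instead keep both pressures with either one sufficing, each would be tested at 0.025. Holding 95% power would then need (2.241 + 1.645)² / (1.960 + 1.645)² = 1.16 times the patients. That is 44 × 1.16 = 51, or 52 in four equal groups, assuming the undisclosed effect size is unchanged.

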### Inclusion criteria

2.4

Hypertensive people between 30 and 80 years old; officially diagnosed with HBP by a medical professional; in stages I and II; and evidenced during ambulatory BP and hypertension monitoring with at least 4 weeks of drug therapy.

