### Exclusion criteria

2.5

Patients who present hypotension before photobiomodulation; pregnant women; glaucoma patients; carriers of electronic implants, such as cardiac pacemakers; epilepsy; seizures; history of neoplasias; and patients with photosensitivity.

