During the study, strategies will be follow to improve adherence to intervention protocols, as nursing consultations in the form of a home visit, or not—at the discretion of the participant. In addition, patients who have a prescription for drug therapy should not suspend it. All patients, regardless of pharmacological or nonpharmacological use, will receive guidelines for the nonpharmacological treatment of hypertension, focusing on the need to maintain a healthy lifestyle, minimizing risk factors for hypertensive disease. These orientations include directions for healthy eating with decreased levels of sodium, fat, and sugar; regular physical exercise with the supervision of a professional; the need for quality sleep of at least 6 to 8 hours; abandonment or diminution of smoking; and the need for stress-minimizing leisure. Patients taking medication will have guidelines regarding the adequate use of medications, respecting the dose and prescribed schedule, reinforced.

Patients have autonomy for discontinue interventions and in this case, they will be replaced, but the same allocation will be remaining. Any outcome data collected from patients will be disconsidered and the participants will remain in ambulatory care.

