### Procedure for data collection, blinding, and photobiomodulation

2.8

A researcher will generate the allocation sequence using the Sealed Envelope Ltd. An examiner will enroll and assign participants to interventions, performing anthropometric assessments, measurement of hemodynamic variables, and blood collection. Other one will be trained to perform the photobiomodulation and will process the blood samples. Other researcher will perform the statistical analyzes of the results without having participated in the collection of data or the application of the procedures. In this way, the last researcher and the patients will be blind. Only after the end of the trial, the participants will know the allocation and results.

A data collection instrument was developed to contain the information needed to achieve the proposed objectives. The variables will be addressed in categories: characterization of the sample, evaluation of risk factors for cardiovascular disease, anthropometric data, data referring to BP measurements, heart rate, biochemical markers before and after photobiomodulation, as well as approach to the use of medicines, diet, and complementary information.

The photobiomodulation will be applied using the Therapy XT laser equipment, brand DMC, Brazil, following the parameters described in Table 1.

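### The 4-week criterion in section 2.4 sets a duration of drug therapy, not an unchanged regimen, so patients whose antihypertensive drug or dose changed just before baseline are eligible

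*Protocol article*

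**What the plan says.** - **Section 2.4 (inclusion).** Hypertension in stage I or II must be "evidenced during ambulatory BP and hypertension monitoring with at least 4 weeks of drug therapy". The closing condition, "with at least 4 weeks of drug therapy", is the only drug-related criterion, and its only number is a minimum duration.
- **Section 2.5 (exclusion).** The list opens with "Patients who present hypotension before photobiomodulation; pregnant women; glaucoma patients; carriers of electronic implants, such as cardiac pacemakers" and goes on to epilepsy, seizures, past neoplasia and photosensitivity. A recent change of antihypertensive treatment is not on it.
- **Section 2.6 (arms).** Each of the four arms "will be submitted to the conventional drug treatment previously instituted", with laser or placebo added. Nothing says how long that treatment must have stood unchanged.
- **Section 2.6 (conduct).** "patients who have a prescription for drug therapy should not suspend it", and patients on medication are reminded to keep to the prescribed dose and timing.
- **Section 2.7 (outcome).** "Measurements of BP (primary outcome) and heart rate will be performed before, during (every 5 minutes), and at the end of each session", with a further measurement at follow-up.
- **Section 2.8 (data collected).** The collection form covers BP and biochemical markers, "as well as approach to the use of medicines, diet, and complementary information". No use of the medicine data for eligibility is stated.
- **Section 2.9 (analysis).** Differences are to be tested both between groups and within groups.

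**The concern.** BP is the primary outcome, and antihypertensive drugs act on it directly. The design adds laser or placebo to a background treatment that is taken as fixed. A 4-week condition serves that purpose only if it concerns the regimen itself. As worded, it can be met by someone whose drug or dose has just been altered and whose BP may still be moving at baseline. That movement would then be recorded during the photobiomodulation cycles.

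Two things are at stake. In the comparison of laser with placebo, the extra movement widens the spread of BP change and may fall unevenly between arms of 11. In the within-group tests there is no control arm to subtract it, so a drug response can be read as a change brought about by the treatment cycles.

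**Working it through.** **1. Does any passage close the gap?** Section 2.4 sets a duration. Section 2.5 excludes no recent change. Section 2.6 continues existing treatment, bars suspending it and reinforces the prescription as it stands; none of this looks back before baseline. Section 2.8 records medicines but does not tie them to eligibility. A patient on drugs for at least 4 weeks with a change the day before B1 meets every listed criterion.

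**2. Is there time for a drug response to show?** Reading the 20 days in section 2.6 as the gap between cycles, and 1 month as 30 days:
- 60-minute arms: 5 + 20 + 5 + 20 + 5 + 30 = 85 days.
- 30-minute arms: 10 + 20 + 10 + 20 + 10 + 30 = 100 days.

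**3. Inputs for the size.** From section 2.3: 11 per arm, significance 5%, power 95%. The article gives no effect size, SD or correlation, so its total of 44 cannot be reproduced; the point does not depend on it. The following are assumptions:
- share f of participants with a recent change: 10% to 30%;
- BP response D still to come after baseline, all in one direction: 5 to 10 mmHg;
- SD of BP change without this component: 10 to 12 mmHg.

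**4. Between arms.** Added variance = f(1 − f)D².
- Low end: 0.1 × 0.9 × 5² = 2.25; 2.25/12² = 1.6%.
- Middle: 0.2 × 0.8 × 8² = 10.24; 10.24/12² = 7.1%.
- High end: 0.3 × 0.7 × 10² = 21; 21/10² = 21%.

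The random part that this adds to an 11-versus-11 difference has SD √(2f(1 − f)D²/11): √(2 × 2.25/11) = 0.64 mmHg to √(2 × 21/11) = 1.95 mmHg.

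For illustration, take a pairwise comparison that had exactly 95% power at 11 per arm (normal approximation). Its power becomes Φ(3.605 × SD/SD′ − 1.96), where SD′ = √(SD² + f(1 − f)D²):
- Low end: SD′ = 12.09, power 0.947, n per arm 11 × 1.016 = 11.2, so 12.
- High end: SD′ = 11.0, power 0.906, n per arm 11 × 1.21 = 13.3, so 14.

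**5. Chance imbalance.** If one arm holds two more recently changed patients than the other, the contrast shifts by 2/11 × 8 = 1.5 mmHg to 2/11 × 10 = 1.8 mmHg. With independent binomial counts at 11 per arm, a gap of two or more has probability 0.27, 0.42 and 0.48 for f = 0.1, 0.2 and 0.3. The standard error of the contrast is 10 × √(2/11) = 4.3 to 12 × √(2/11) = 5.1 mmHg, so the shift is about 0.3 to 0.4 standard errors. It is one realisation of the variance in step 4 and must not be counted on top of it.

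**6. Within a group.** The mean change moves by f × D with no laser effect: 0.1 × 5 = 0.5 mmHg to 0.3 × 10 = 3.0 mmHg. The standard error is SD′/√11:
- Low end: 12.09/√11 = 3.65; shift 0.5/3.65 = 0.14 standard errors.
- High end: 11.0/√11 = 3.32; shift 3.0/3.32 = 0.90 standard errors.

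A paired t test with 10 degrees of freedom at a nominal 5% would then reject in about 5.2% to 13% of trials (noncentral t).

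**7. Within a session.** If a 10 mmHg response is spread evenly over 28 days (assumed), the drift in one 60-minute session is 10/(28 × 24) = 0.015 mmHg, which is negligible.

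**The case against.** The strongest reply concerns weight, and most of it stands.

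- **Randomisation.** A reader might infer that recent drug changes bias the comparison of laser with placebo. The documents do not support that. Allocation is randomised in blocks, each laser arm has a placebo arm on the same schedule, and recent changes balance in expectation. What is left is noise and chance imbalance.
- **Frequency.** A reader might also infer that recent adjustment is the usual case in this population. Section 2.1 says only that participants are followed medically at an outpatient clinic. No passage says how often regimens had just changed.
- **Assumed size.** Share, response and SD are all assumptions. A change made two or three weeks before baseline leaves only part of its response to come, and the SD used for planning may already include ordinary drug adjustment. The low end, under 2% added variance, is credible.
- **Part of the outcome is spared.** Change from before to after a single session is barely touched.
- **Intent.** Section 2.6 asks for adherence to the prescription and continues existing treatment, which shows a wish to hold background drugs constant. It does not rule out a prescriber's change before baseline.
- **Condensation.** How stability is checked at screening may sit in a fuller protocol. This has less force, because the article states the criterion itself, with a number, and that number is attached to duration of therapy.

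The reply does not reach the within-group tests, which randomisation does not protect.

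**Conclusion.** The point holds in a limited form. Section 2.4 admits patients with a recently changed regimen, while section 2.6 relies on background treatment being constant. For the randomised comparison the cost is precision: about 1.6% to 21% more variance in BP change, with no systematic bias. For the within-group tests over cycles and at follow-up, the group mean can be displaced by 0.5 to 3.0 mmHg without any laser effect. These figures rest on an assumed 10% to 30% share of recent changes, a residual response of 5 to 10 mmHg and an SD of change of 10 to 12 mmHg; none of these is in the article. Change within a session is largely unaffected. This is a cheap improvement to a stated criterion, not a flaw that invalidates the trial.

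A related inconsistency should be reconciled in the same edit. Section 2.4 requires drug therapy, but section 2.6 says "All patients, regardless of pharmacological or nonpharmacological use, will receive guidelines for the nonpharmacological treatment of hypertension" and speaks of those who have a prescription as a subset.

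**What to change.** Reword the drug criterion in section 2.4 so that the protocol's own 4-week period applies to antihypertensive drugs and doses unchanged before the B1 measurement. The sponsor may set another period; the documents do not show which is sufficient. Confirm eligibility from the medicine data already collected under section 2.8, and let a patient who fails only on this point be re-screened. In the same edit, reconcile sections 2.4 and 2.6 on whether patients without drug therapy can take part.

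The cost is one line of text and a delay of up to 4 weeks for recently adjusted candidates. March to August 2019 is 184 days. If that window must hold the whole study, a 100-day course leaves 184 − 100 = 84 days for enrolment, and 28 days is a third of that, so the delay should be weighed for the candidates concerned. The change does not cover drug changes after baseline, and it alters no patient's care.
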